# Unresectable Intermediate-Size (3–5 cm) Colorectal Liver Metastases: Stereotactic Ablative Body Radiotherapy Versus Microwave Ablation (COLLISION-XL): Protocol of a Phase II/III Multicentre Randomized Controlled Trial

**DOI:** 10.1007/s00270-023-03498-8

**Published:** 2023-07-10

**Keywords:** Colorectal cancer, Colorectal liver metastases (CRLM), Liver metastases, Thermal ablation, Microwave ablation (MWA), Radiotherapy, Stereotactic body radiotherapy (SBRT), Randomized controlled trial (RCT)

## Abstract

**Background:**

Although microwave ablation (MWA) has a low complication rate and good efficacy for small-size (≤ 3 cm) colorectal liver metastases (CRLM), local control decreases with increasing size. Stereotactic body radiotherapy (SBRT) is gaining interest as a potential means to treat intermediate-size CRLM and might be less susceptible to increasing volume. The objective of this study is to compare the efficacy of MWA to SBRT in patients with unresectable, intermediate-size (3–5 cm) CRLM.

**Methods:**

In this two-arm, multicentre phase II/ III randomized controlled trial, 68 patients with 1–3 unresectable, intermediate-size CRLM suitable for both MWA and SBRT, will be included. Patients will be treated with MWA or SBRT as randomised. The Primary endpoint is local tumour progression-free survival (LTPFS) at 1 year (intention-to-treat analysis). Main secondary endpoints are overall survival, overall and distant progression-free survival (DPFS), local control (LC) and procedural morbidity and mortality and assessment of pain and quality of life.

**Discussion:**

Current guidelines lack clear recommendations for the local treatment of liver only intermediate-size, unresectable CRLM and studies comparing curative intent SBRT and thermal ablation are scarce. Although safety and feasibility to eradicate tumours ≤ 5 cm have been established, both techniques suffer from lower LTPFS and LC rates for larger-size tumours. For the treatment of unresectable intermediate-size CRLM clinical equipoise has been reached. We have designed a two-armed phase II/ III randomized controlled trial directly comparing SBRT to MWA for unresectable CRLM 3–5 cm.

***Level of Evidence*:**

Level 1, phase II/ III Randomized controlled trial.

*Trial Registration*: NCT04081168, September 9th 2019.

**Graphical Abstract:**

[figure not shown]

## Introduction

Colorectal carcinoma is one of the most common malignancies, with 1.8 million new cases worldwide in 2018 [1]. In the course of the disease roughly 30–50% of patients develop colorectal liver metastases (CRLM) [2, 3]. Although chemotherapeutic regimens are improving, local therapy remains the only option associated with a realistic chance of long-term disease control or in selected cases even cure. Surgical resection represents the historical standard and treatment of first choice with 5-year overall survival (OS) reaching 40–55% [5, 6]. However, only a minority of the patients (20–30%) is eligible for surgery, due to insufficient future liver remnant after resection, unfavourable anatomical location of the metastases, concomitant co-morbidities or patients with previous extensive abdominal surgery [7]. For the eradication of liver only and limited unresectable metastases, several ablative strategies have emerged.

Thermal ablation (i.e., radiofrequency ablation (RFA), microwave ablation (MWA)) for small liver tumours has an excellent safety profile with a low complication rate and it offers good local control. Local tumour progression (LTP) rates range 0–10% after thermal ablation for tumours ≤ 3 cm [8–12]. However, in tumours > 3 cm the efficacy rapidly decreases, with LTP rates ranging 14–45% [8, 9, 13]. For these larger-size tumours, novel MWA generation systems or tumour-bracketing multi-probe ablation techniques are preferred. Stereotactic body radiotherapy (SBRT) is gaining more interest as a potential treatment method for intermediate-size CRLM. A recent propensity score-based comparison favoured SBRT over thermal ablation for CRLM > 3 cm regarding local control after initial treatment [16]. Yet it seems unjust to compare local control rates following only one ablative procedure, of a one-shot treatment method (SBRT), with an easily repeatable technique (MWA).

This multi-centre phase-II/ III randomized controlled trial was designed to compare the efficacy of SBRT versus MWA in unresectable intermediate-size (3–5 cm) CRLM. The aim is to prove superiority of SBRT or MWA regarding to 1 year local tumour progression free survival.

## Design

### Design

The COLLISION-XL trial is a phase II/III, multicentre randomized controlled trial initiated by the Amsterdam University Medical Centres (Amsterdam UMC, location VUmc in Amsterdam, the Netherlands) and endorsed by the Dutch Colorectal Cancer Group (DCCG). Patients will be recruited in at least five hospitals in the Netherlands: Amsterdam UMC (location VUmc), Amsterdam; Ziekenhuis Gelderse Vallei (ZGV), Ede; University Medical Centre Groningen (UMCG), Groningen; Noordwest hospitals, Alkmaar; Medical centre Leeuwarden, Leeuwarden. The trial is investigator-initiated and funded by a partially restricted grant from Johnson & Johnson and registered at clinicaltrials.gov under NCT04081168. The protocol has been approved by the medical Ethical Review Board (METc) of the Amsterdam UMC, location VUmc (no. 2019.262–NL68326.029.19). The trial will be conducted in accordance with the Declaration of Helsinki and the guidelines for Good Clinical Practice (GCP). The duration of the study will be around 4 years (3 years for inclusion and 1 year follow-up). The flow chart of the study design is shown in Fig. 1.

**Fig. 1 Fig1:**
[figure not shown]
Flowchart of the study design

### Inclusion Criteria

Patients with 1–3 unresectable intermediate-size CRLM, suitable for both MWA and SBRT are eligible to participate. An overview of inclusion and exclusion criteria is listed in Table 1. Additional CRLM are allowed if they are either resectable or < 3 cm and amenable for thermal ablation. In total, a maximum of 10 CRLM without extrahepatic disease or 5 CRLM in case of limited extrahepatic disease is allowed. Prior focal liver treatment is allowed, but resection or ablation site recurrences are disqualified as target lesions. Patients without prior focal liver treatment should be either unsuitable for 1st line systemic therapy or have progressed under/after 1st-line systemic therapy. Potential candidates will be registered and undergo routine pre-procedural work-up: baseline full blood examination, ceCT of the chest and abdomen and either an upper abdominal ceMRI or a total body ^18^F-FDG PET-CT.

**Table 1 Tab1:** Inclusion and exclusion criteria

Inclusion criteria	Exclusion criteria
Histological documentation of primary colorectal tumour	No target lesions suitable for both ablation and SBRT
Age > 18 years	Chemotherapy ≤ 6 weeks prior to the procedure
1–3 unresectable CRLM size 3–5 cm eligible for both MWA and SBRT (target lesions)	Immunotherapy ≤ 6 weeks prior to the procedure
Additional CRLM are allowed if considered either resectable, or ablatable and < 3 cm	Severe allergy to contrast media not controlled with premedication
No or limited extrahepatic disease (1 extrahepatic lesion is allowed, not including positive para-aortal lymph nodes, celiac lymph nodes, adrenal metastases, pleural carcinomatosis or peritoneal carcinomatosis)	Compromised liver function (e.g. signs of portal hypertension, INR > 1,5 without use of anticoagulants, ascites)
For subjects with liver only disease the maximum number of CRLM is 10; for subjects with limited extrahepatic disease the maximum number of CRLM is 5	Radical treatment unfeasible or unsafe (e.g. insufficient future liver remnant [FLR])
Resection for additional resectable lesions is allowed when considered possible obtaining negative resection margins (R0) and preserving adequate future liver remnant	Pregnant or breast-feeding subjects
Prior focal liver treatment is allowed, but resection or ablation site recurrences are disqualified as target lesions	
Unsuitable for (further) systemic therapy	
Written informed consent	

Participants will be stratified according to presence of extrahepatic disease and whether patients will undergo surgical resection. An experienced expert panel, consisting of at least two interventional radiologists, two hepatobiliary surgeons and two radiation oncologists, will determine whether the CRLM are (un)resectable and/or (un)ablatable. Unresectable intermediate-size CRLM suitable for both MWA and SBRT are so-called target-tumours. All additional non-target tumours should be resectable or, if unresectable and ≤ 3 cm, eligible for thermal ablation.

### Exclusion Criteria

Patients are considered ineligible and will not be randomized pre-procedurally or during surgical inspection or IOUS if (1) the maximum amount of CRLM is exceeded, (2) there are no target tumours, (3) impermissible extrahepatic disease is present or (4) radical treatment is no longer feasible. Pre-procedurally appointed target tumours that prior to randomization prove to be suitable for resection or unsuitable for either MWA or SBRT during surgery, are no longer regarded as target tumours, potentially excluding patients from further study participation.

### Statistics

Given the unknown 1 year LTP rate for intermediate-size CRLM for both techniques, it was not possible to apply validated assumptions for both proportions. Hence a difference in 1y-LTP rate of more than one third (33%) is considered clinically relevant as it seems unlikely that a smaller difference will significantly impact overall survival. Most 1-year LTP will either be re-ablated or patients will receive systemic chemotherapy because of the simultaneous presence of extensive distant progression. In other words, unablatable LTP at 1-year without recurrence at distant sites is uncommon. We therefore accept that a difference in 1 year LTPFS of more than one third (0.33) will reject the null hypothesis concluding that the techniques are significantly different [17]. Group sample sizes of 33 in group 1 and 33 in group 2 achieve 81.059% power to detect a difference between the group proportions of −0.33. The proportion in group 1 (the treatment group) is assumed to be 0.665 under the null hypothesis and 0.3350 under the alternative hypothesis. The proportion in group 2 (the alternative treatment group) is 0.665. The test statistic used is the two-sided Z-test with un-pooled variance. The significance level of the test is 0.05. To account for a 3% loss to follow-up (= 2 patients) we need to randomize 34 patients (NR) into each of the two arms.

Baseline patient-, tumour- and treatment characteristics will be described and compared between the two treatment arms using the Chi-square test for categorical variables and the independent two-sample t-test, ANOVA or Mann–Whitney-U-test for continuous variables. *P* values below 0.05 will be considered significant. When appropriate, box-plots and cross-tables will be used for descriptive statistics of continuous and categorical variables, respectively. One year LTPFS rates will be compared between MWA and SBRT using the Chi square test. To determine hazard ratios (HR) for multivariate analysis, logistic regression will be used. Univariate LTPFS time analysis will be performed using the Kaplan–Meier method with corresponding two sided 95% confidence intervals (CI). Differences in LTPFS length will be analysed using the log rank test.

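### The 81.059% power is derived for an un-pooled Z-test, not for the planned chi-square test, and the sentence on 0.33 is worded as a rejection rule

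*Protocol article*

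**What the plan says.** Everything at issue is in the Statistics section of the protocol article.

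- Power: "Group sample sizes of 33 in group 1 and 33 in group 2 achieve 81.059% power". The group 1 proportion "is assumed to be 0.665 under the null hypothesis and 0.3350 under the alternative hypothesis", and for group 2: "The proportion in group 2 (the alternative treatment group) is 0.665".
- Test behind that power: "The test statistic used is the two-sided Z-test with un-pooled variance". Level: "The significance level of the test is 0.05".
- Planned primary comparison, one paragraph later: "One year LTPFS rates will be compared between MWA and SBRT using the Chi square test". The article does not say whether a continuity correction applies.
- Meaning of 0.33: "We therefore accept that a difference in 1 year LTPFS of more than one third (0.33) will reject the null hypothesis". Just before this, a difference of more than one third is called clinically relevant.
- Numbers randomized: 34 per arm, to allow for the loss of two patients. The Randomization section says that all randomized patients are analysed in their assigned group.

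**The concern.** Two things do not line up.

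First, the power belongs to a Z-test with un-pooled variance, while the primary comparison is a chi-square test. Uncorrected, the chi-square is the Z-test with pooled variance. Pooling makes the standard error larger when the two proportions differ, so the same approximation returns a lower power. With a stated figure only one point above 80%, the choice of test decides on which side of 80% the design falls.

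Second, the sentence on 0.33 has the form of a decision rule, yet the same section sets a 0.05 level and a chi-square test, which has a different and smaller critical difference. A reader of the final report could ask which of the two governs a significant result with an observed difference between about 0.24 and 0.33.

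**Working it through.** **Inputs** (all from the Statistics section): 33 per arm; proportions 0.335 and 0.665; difference 0.33; two-sided level 0.05, so z = 1.960. The outcome is taken as one independent yes/no result per patient, as the sample size calculation does.

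**1. The printed figure.** Un-pooled standard error: sqrt(2 × 0.335 × 0.665 / 33) = 0.1162. Power = Φ(0.33/0.1162 − 1.960) = Φ(0.880) = 0.8106. This agrees with 81.059%, so the arithmetic is right for the test it names.

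**2. The same approximation for the planned test.** The pooled proportion is 0.5, so the pooled standard error is sqrt(2 × 0.5 × 0.5 / 33) = 0.1231. Power = Φ((0.33 − 1.960 × 0.1231)/0.1162) = Φ(0.764) = 0.777. By this formula 80% needs 35 per arm.

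**3. Exact power.** All pairs of binomial outcomes were enumerated under 0.335 versus 0.665:

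| Evaluable per arm | Chi-square, uncorrected | Un-pooled Z |
|---|---|---|
| 32/32 | 79.3% | 79.3% |
| 32/33 | 76.7% | 77.1% |
| 32/34 | 78.4% | 81.3% |
| 33/33 | 81.25% | 81.25% |
| 33/34 | 78.7% | 79.0% |
| 34/34 | 77.5% | 83.1% |
| 35/35 | 78.5% | 84.7% |

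Of these sizes, only 33/33 takes the chi-square above 80%. There its exact type I error is 5.4% at a common proportion of 0.665 and 6.4% at 0.5. The expected loss of two patients gives 33/33 only if one is lost from each arm.

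With the continuity correction, exact power is 73.6% at 33/33 and 70.1% at 34/34. Fisher's test gives the same values.

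The two tests can disagree on real data. With 13/34 versus 21/34, the difference is 8/34 = 0.235. The pooled z is 1.940 (p = 0.052, not significant). The un-pooled standard error is sqrt(2 × 0.3824 × 0.6176 / 34) = 0.1179, so z = 0.2353/0.1179 = 1.996, which is significant.

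**4. The 0.33 sentence.** Near a pooled proportion of 0.5, the chi-square's critical difference at 33 per arm is 1.960 × 0.1231 = 0.241. By enumeration, every difference of 8/33 (0.242) or more rejects at 33/33; for example, 12/33 versus 20/33 gives p = 0.049. The largest difference that can fail to reject is 7/33 (0.212) at 33/33 and 8/34 (0.235) at 34/34.

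If an observed difference above 0.33 were required, the normal approximation gives 50% power when the true difference is 0.33. Exact values are 54.6% at 33/33 and 47.7% at 34/34, with a type I error below 1%. Under the planned alternative, the chi-square is significant while the observed difference is 0.33 or less in 26.6% (33/33) or 29.8% (34/34) of trials.

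**The case against.** A reader might infer that the planned chi-square simply has 78% power and that 81.059% is an error. The documents do not support that. The figure is correct for the test it names. At the stated 33 per arm, the uncorrected chi-square and the un-pooled Z reject on practically the same outcomes, and both have an exact power of 81.25%, within 0.2 points of the printed value. The 6.4% type I error at that size is also shared by both tests, and is 5.4% under the article's own null of 0.665. The 70% to 74% figures apply only if a correction is used, which the article does not state. All of this stands. It does not remove the point, because 33/33 is a favourable spot in a discrete distribution, and the chi-square is below 80% at every other size checked.

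A reader might also infer that the article lays down two contradictory rejection rules. It does not go that far. The sentence says that a difference above 0.33 will reject, not that only such a difference will. Read that way it is true: no observed difference above 0.33 is non-significant at 33/33 or 34/34. The surrounding text, with its clinically relevant difference, its power for 0.33 and its 0.05 level, suggests loose wording for the target difference. What stands is that the wording is that of a decision rule and that nothing in the section rules out the threshold reading.

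**Conclusion.** The point holds in a limited form. The stated power is not derived for the test that will be run. For the uncorrected chi-square it is 77.7% by the same approximation. Exactly, it is 81.25% at 33/33 and 76.7% to 79.3% at the other sizes checked, with 77.5% if all 34 per arm are evaluable. The shortfall against the printed figure is therefore between nothing and about four points, and larger (70% to 74% power) if a continuity correction is applied. The 0.33 sentence is not false, but it reads as a threshold that would roughly halve the chance of success (48% to 55% power).

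These figures rest on the article's own proportions, independent patient-level outcomes and a two-sided 0.05 level. This is a moderate correction and does not undermine the design.

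**What to change.** Name one primary test and state whether a continuity correction is used. Give the power for that test. For the uncorrected chi-square, for example: *about 78% by normal approximation for 0.665 versus 0.335 at 33 per arm; exact power 81% at 33/33 and 77.5% at 34/34*.

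Reword the 0.33 sentence so that 0.33 is the clinically relevant target difference on which the sample size is based, and state separately that the null hypothesis is rejected if p<0.05 in the named test.

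The cost is wording only. The stated power becomes slightly less favourable, and no extra patients are needed.

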## Abbreviations

^18^F-FDG: [18F]-fluoro-2-deoxy-D-glucose
COLLISION XL: Unresectable colorectal liver metastases: stereotactic body radiotherapy versus microwave ablation
Ce: Contrast-enhancement
CI: Confidence interval
CRC: Colorectal cancer
CRLM: Colorectal liver metastases
CT: Computed tomography
DPFS: Distant progression-free survival
HR: Hazard ratio
IRE: Irreversible electroporation
LC: Local tumour control
LTP: Local tumour progression
LTPFS: Local tumour progression-free survival
MRI: Magnetic resonance imaging
MWA: Microwave ablation
OS: Overall survival
PET: Positron emission tomography
RCT: Randomized controlled trial
RFA: Radiofrequency ablation
SBRT: Stereotactic body radiotherapy

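### Logistic regression is named as the source of hazard ratios, but it gives odds ratios; measure and model must be made to agree

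*Protocol article*

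**What the plan says.** The Statistics section of the protocol article lists the analyses of local tumour progression-free survival (LTPFS) in this order:

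- The 1-year comparison: "One year LTPFS rates will be compared between MWA and SBRT using the Chi square test".
- The multivariable analysis: "To determine hazard ratios (HR) for multivariate analysis, logistic regression will be used".
- The time-to-event description: "Univariate LTPFS time analysis will be performed using the Kaplan–Meier method", with two-sided 95% confidence intervals.
- The time-to-event test: "Differences in LTPFS length will be analysed using the log rank test".

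The Abbreviations section expands the term as "HR: Hazard ratio", so HR is not a private label for some other ratio. No Cox model or other model for the hazard appears in the article. The multivariable sentence does not name its endpoint or covariates, and it does not say whether treatment is the term of interest.

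**The concern.** Logistic regression models the odds that a yes/no outcome has occurred. Its exponentiated coefficient is an odds ratio. It needs a known status at the chosen time for every unit, and it uses neither the time of an event nor partial follow-up. A hazard ratio compares event rates over time and needs a time-to-event model. A pooled discrete-time logistic model can approximate a hazard ratio, but the article describes none.

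Two things are at stake. First, a reader who meets an odds ratio labelled as a hazard ratio will take the association to be stronger than it is, because the two measures separate when events are common. Second, the sentence does not fix which adjusted analysis was planned. A Cox model and a logistic model with odds ratios would each correct half of it, and if nothing is settled the choice stays open until the data are seen.

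**Working it through.** **Inputs**, from the Statistics section unless noted:

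- Group 1 proportion: "is assumed to be 0.665 under the null hypothesis and 0.3350 under the alternative hypothesis".
- Group 2 proportion: "The proportion in group 2 (the alternative treatment group) is 0.665".
- Size and power: "Group sample sizes of 33 in group 1 and 33 in group 2 achieve 81.059% power", two-sided Z-test with unpooled variance, significance level 0.05.
- Local progression after thermal ablation of tumours above 3 cm: 14% to 45% (Introduction).
- The pairs 45% against 30%, 30% against 20% and 20% against 14% are my illustrations; the document does not state them as pairs.

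**Step 1: reproduce the plan's own figure.**

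Standard error = √(0.335 × 0.665/33 + 0.665 × 0.335/33) = √0.013502 = 0.1162.

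Power = Φ(0.33/0.1162 − 1.960) = Φ(0.880) = 81.059%, which matches the stated power. The calculation uses only the two proportions and no regression model, so the multivariable sentence has no bearing on the sample size.

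**Step 2: odds ratio and hazard ratio from the same 1-year risks.**

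For 1-year event risks p₁ and p₂:

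- Odds ratio, which logistic regression estimates: OR = [p₁/(1 − p₁)] / [p₂/(1 − p₂)].
- Hazard ratio under proportional hazards, with no censoring before 1 year: HR = ln(1 − p₁)/ln(1 − p₂).

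At the planning values:

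- OR = (0.665/0.335)/(0.335/0.665) = 3.94.
- HR = ln(0.335)/ln(0.665) = (−1.0936)/(−0.4080) = 2.68.
- OR/HR = 3.94/2.68 = 1.47.

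With the groups reversed, the values are 0.25 and 0.37. The two planning proportions sum to 1, so the pair of event risks is the same whether they are read as progression rates or progression-free rates.

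**Step 3: how the gap depends on the event rates.**

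| 1-year event risks | OR | HR | OR/HR |
|---|---|---|---|
| 66.5% vs 33.5% (planning values) | 3.94 | 2.68 | 1.47 |
| 45% vs 14% (ends of the range in the Introduction) | 5.03 | 3.96 | 1.27 |
| 45% vs 30% (illustration) | 1.91 | 1.68 | 1.14 |
| 30% vs 20% (illustration) | 1.71 | 1.60 | 1.07 |
| 20% vs 14% (illustration) | 1.54 | 1.48 | 1.04 |

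Under these assumptions the direction is always the same. As p rises, log odds change at rate 1/[p(1 − p)], and the log cumulative hazard changes at rate 1/[(1 − p)(−ln(1 − p))]. Since −ln(1 − p) exceeds p, the log odds always change faster, so the odds ratio is always further from 1. These are two-group values without covariates.

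**The case against.** The strongest reply is that only a word is wrong. The sentence comes straight after the Chi-square comparison of 1-year rates and before the Kaplan–Meier and log-rank methods, and logistic regression is an ordinary adjusted companion to a binary 1-year endpoint. On that reading the model is sound and the label should be odds ratio. This is a fair reading, and the text does not rule it out. Nor does it rule out that Cox regression was meant. Either way, the sentence needs correcting.

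A second reply is that an article condenses a fuller protocol. That would excuse a missing detail. Here the article makes a positive statement that pairs a named model with a measure that the model does not give.

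Three stronger readings are tempting, and the document does not support them:

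- **A reader might infer that the primary result is compromised.** It is not. The primary comparison is a Chi-square test of 1-year rates, and neither it nor the sample size uses this model. With no association, the odds ratio and the hazard ratio both equal 1, so the wrong label does not create false positives.
- **A reader might infer that adjusted and unadjusted hazard ratios would clash.** The plan attaches no hazard ratio to Kaplan–Meier or the log-rank test, so there is no unadjusted ratio under the same label to conflict with.
- **A reader might infer that the treatment effect will be overstated by 47%.** The sentence does not say that treatment is the term of interest, and an odds ratio misleads only when read as a hazard ratio. The 47% also belongs to planning proportions that the Statistics section says could not be validated. Its literature range for thermal ablation is lower, and recurrences successfully retreated with the same technique within 6 months are not counted as events (Outcome Measures), which lowers the counted rates further.

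**Conclusion.** The point holds as a mismatch between measure and model: the article plans hazard ratios from a model that gives odds ratios, and names nothing else that could supply them. If the estimates were reported as hazard ratios, they would be too far from 1. In the cases worked, the excess runs from about 4% (20% against 14%) through 14% (45% against 30%) to 47% (planning proportions). These figures assume proportional hazards and no censoring before 1 year. The excess that would actually occur depends on event rates that the protocol treats as unknown.

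This should be fixed, but it concerns a supporting analysis. The document does not show whether the model or the label is the slip, so the correction should not presume either.

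**What to change.** Replace the sentence with one of the following, and settle the choice before outcome data are analysed:

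- **If hazard ratios are wanted:** state that adjusted hazard ratios for LTPFS will be estimated with a Cox model. If the unit is the tumour, add patient-clustered robust variance. Outcome Measures defines the endpoint per treated tumour, and the inclusion criteria allow one to three target tumours per patient, so the replacement sentence has to say how the variance is obtained.
- **If the 1-year status is wanted:** keep logistic regression, state that its outcome is 1-year LTPFS status, and report the results as odds ratios.

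The cost is one sentence in the protocol or analysis plan. It needs no new data and no change to the sample size, the visits or the primary test.
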